   *** **Possible Side Effects/Risks and Countermeasures**

Anal fissure, rectal prolapse, and perianal burns have been reported as adverse events or side effects from the use of a bidet. Most of these cases are high-risk patients with abnormalities in the perianal nerves due to long-term use of the bidet, old age, or diabetes, or it is caused by using water above 50°C [10-12].

Side effects of sitz baths can also be similar to bidets, but the possibility is very low. Therefore, these side effects occur very rarely, but safety evaluation will be made through an outpatient interview or anal examination during clinical trials. When side effects occur, immediate treatment will be performed, and the appropriate treatment cost for this will be supported by the study.

In addition, side effects from anal surgery may occur, which may vary from pain in the wound to simple infections, abscesses, anal fistulas, fecal incontinence, and urinary retention. This will also be evaluated through an outpatient examination, and immediate treatment will be provided when it occurs. However, treatment costs for this are not supported.

Pain that occurs after anal surgery can be significantly reduced with a sitz bath or bidet. For additional pain control, this study planned to use the amount of analgesics commonly used after surgery. However, if the pain is not controlled by the use of these analgesics, it is thought that the occurrence of complications should be suspected. It is considered reasonable to identify complications through outpatient care and decide whether to continue the clinical trial. If the pain persists despite appropriate treatment, it is thought that the dropout of the patient should be considered.

***** **A description of the rationale (or expected scientific/medical benefit) that the study should be conducted despite the predicted side effects/risk**

The sitz bath is widely used in the treatment of anal diseases, but it is an undeniable fact that it is a very difficult treatment process for patients with discomfort after surgery. If a bidet can be a substitute for a sitz bath, it will be a more convenient way after anal surgery as an auxiliary method. To this end, it can be said that a study comparing the pain control and wound healing effects between sitz bath and bidet in patients after surgery is essential.

1. **Criteria for Discontinuation and Dropout**
2. When side effects occur due to anal surgery
3. In case of side effects of sitz bath or bidet
4. When another serious disease occurs during clinical trial and treatment is necessary
5. Others, If clinical trials cannot be performed properly
6. When the subject withdraws the consent of participating in the clinical trial
7. **Safety Evaluation Criteria including Side Effects, Evaluation Method, and Reporting Method**

After anal surgery, an outpatient visit is performed every week for visual anal inspection and palpation. Through this, the adverse events or side effects that may occur due to the bidet or sitz bath are evaluated, and the examination is conducted considering the possibility of anal fissure, rectal prolapse, and perianal burns.

If an adverse event or side effect occurs, document and report it to the IRB, and report any serious adverse event (SAE) immediately. A serious adverse event is defined as any unintended medical phenomenon that occurs in a subject during a clinical trial and is as follows.

1. If it causes death.
2. If it is life-threatening: The meaning of life-threatening refers to the case where the investigator determines that the patient is at risk of death at the time of the event, and it does not include adverse events that may lead to death if it becomes more serious.
3. If hospitalization or prolongation of the hospitalization period is required
4. If permanent or serious disability and dysfunction were induced
5. If congenital anomalies or birth defect in the offspring of the study subjects (male or female) who received the investigational product
6. Reactions that jeopardized subjects or that require medical or surgical treatment to prevent the results listed above, even if they are not included in the criteria listed above for the seriousness.
7. **Data Safety Monitoring Plan (DSMP)**

The person in charge of monitoring (department of surgery, professor [name]) should regularly (once/year) confirm that the protocol and GCP are being complied with and review the source data to verify that the information in the CRF is accurate. The patient's handwritten VAS and CRF should be confirmed to be consistent.

Also, in conducting this clinical trial, the subjects' evaluation results will be continuously monitored by the principal investigator and safety monitoring will be performed with the help of MRCC in case of a problem. If an adverse event is reported, an immediate report will be made to the IRB and the continuation of the clinical trial will be determined according to the severity of the adverse event.

Recruitment of study subjects, consent process, data analysis, and report preparation for this study will be conducted under the supervision of the person in charge of monitoring who has no conflict of interest with this study.

1. **Data Analysis and Statistical Analysis Method**

Data and statistical analysis will be conducted with the help of MRCC.

Establishment of analysis set: Data analysis is performed by dividing the full analysis set (FAS) and the PP set.

According to ICH E9, FAS is an analysis set that is as close as possible to the concept of the intention-to-treat (ITT) principle and it can exclude the least number of subjects from the analysis for justifiable reasons from all randomized subjects. The reasons for excluding a subject from the analysis target group without the possibility of introducing bias are under the following circumstances.

① Subjects who violate the criteria for inclusion/exclusion of subjects

② Subjects who have never received the study drug

③ Subjects with no data after randomization

In the case of ② and ③, the excluded subjects were due to dropout caused by schedule adjustments with the visiting technician during the installation of a bidet after surgery, and it is expected that there is no relation to the treatment effect. However, to determine whether there are potential biases that may occur by excluding them, we will check whether the underlying characteristics collected during the screening process differ from those included in the analysis.

The PP set consists of subjects who performed sitz baths or bidets as assigned to at least 80% of the set schedule.

The primary endpoint is determined by the FAS.

Analysis of the underlying characteristics and questionnaire of the two groups: Continuous variables are presented using t-test and categorical variables are compared using the chi-squared test. Pain scores are compared for each week using a t-test. Bonferroni correction is implemented in consideration of the expansion of Type I error due to multiple comparisons. For the pain score in the first week after surgery, it is confirmed that the upper limit of 95% of the bidet group is less than the value 10% higher than the average value of the sitz bath group.

Analysis of adverse events and side effects: Identify the frequency of each side effect and check whether there is a significant difference between the two groups through the Fisher test. Analysis of side effects will be performed on all subjects who have conducted a bidet or sitz bath even once.

A statistical test is conducted in a two-tailed test and a p-value less than 0.05 is considered significant.

1. **Study Schedule**

|  | December | January | February | March | April | May | June | July | August | September | October | November |
| --- | --- | --- | --- | --- | --- | --- | --- | --- | --- | --- | --- | --- |
| Building a network of participating hospitals |  |  |  |  |  |  |  |  |  |  |  |  |
| Recruitment of subjects |  |  |  |  |  |  |  |  |  |  |  |  |
| Clinical trial |  |  |  |  |  |  |  |  |  |  |  |  |
| Results analysis and interim reporting |  |  |  |  |  |  |  |  |  |  |  |  |
| Preparation of paper |  |  |  |  |  |  |  |  |  |  |  |  |
| Paper presentation and result report |  |  |  |  |  |  |  |  |  |  |  |  |

1. **Measures for the Safety Protection of the Subjects**
2. **Basic Principal for Ensuring Research Ethics**

This study will comply with the Helsinki Declaration and ICH-GCP revised in 2013 and will be conducted following the protocol approved by the Institutional Review Board (IRB). The purpose and content of the study are explained to the subjects, and only applicants who know and consent to the purpose of this study will participate in the study. Participants in the study can discontinue the trial at any time during the trial and also have been aware of this. There are no special disadvantages to participants related to this study, and the confidentiality of medical information will be maintained. Documents containing the patient's personal information will be retained by encrypting and enclosing in the office of the professor in charge. Access is prohibited except for the investigators involved in this study.

1. **Subjects’ Consent Process**

Before surgery, the medical staff will explain the risks and benefits of this study in the ambulatory care of the department of surgery, and then obtain consent to participate in the study. The principal investigator or sub-Investigators obtains informed consent, and only adult patients who are able to understand and perform this clinical trial are included. Consent can be obtained immediately after explaining the study, and if necessary, it can be obtained at an outpatient visit right before surgery, or when hospitalized for surgery. After sufficient explanation of the study, allow patients to decide by themselves to consent. The investigator explains to the patient in easy words, and the consent form is also explained in an easy-to-understand manner.

1. **Compensation Plan for Subjects**

The subject will receive an amount of 50,000 won as compensation per outpatient visit after surgery, and the initial participation fee (100,000 won) will be supported by the research fund. It is not obliged to participate in the study until the end, but the compensation will be paid differentially if the final termination is not made (total amount of 300,000 won upon completion, but 500,000 won for Daehang Hospital). Also, in the event of side effects caused by a bidet or sitz bath, the appropriate treatment cost will be borne by the investigator.

Study subjects will receive free support for bidet installation or sitz bath.

1. **Confidentiality of Subjects’ Personal Information**

1) The name of the subject is anonymized with initials, and the subject identification and record number are encrypted to be managed by the principal investigator in a separate file so that personal information is not exposed.

2) The use of results or providing them to others for purposes other than the original purpose of this study is limited only if the subject consent in writing. At this time, whether personal information is included depends on the consent of the subject.

3) If the subjects or their legal representative of this study applies requests to access or issue a copy of test results, records regarding the objections, the informed consent form, it should be responded to.

4) In this study, files containing the subject's personal information and examination results will be encrypted and retained, which will only be accessible to the investigator and co-investigators.

5) Samples will be managed and handled by assigning a study participation number that cannot identify individuals.

6) Under Article 15 of the Enforcement Regulations of the Bioethics and Safety Act, records related to the study are kept for 3 years from the end of the study, and documents that are past the retention period are destroyed according to Article 16 of the Enforcement Decree of the Personal Information Protection Act.

1. **Additional protective measures in case of including vulnerable subjects**

(N/A)

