4. Secondary endpoint- questionnaires on the degree of urinary difficulty improvement (IPSS), men over 40 years old (subgroup analysis)
5. **Efficacy Evaluation Criteria, Evaluation Method**
6. Primary endpoint evaluation method – The degree of subjective pain is evaluated by the Visual Analog Scale (VAS). The patient records the degree of pain after taking a sitz bath or bidet at a certain time every day (right after waking, 7-8 am). After a week, the degree of pain (after using a sitz bath or bidet immediately after waking up) is used as the primary endpoint for comparative analysis.
7. Secondary endpoint evaluation method- Also, the degree of pain reduction is performed the linear comparative analysis as a continuous variable.
8. Secondary endpoint evaluation method - Every week after anal surgery, the outpatient clinic visit is made to get an anal examination. The physician in the outpatient clinic should confirm complete epithelialization and no exudate from the anal wound through visual inspection and palpation, and it is determined as a complete healing.
9. Secondary endpoint evaluation method – Convenience in performing sitz baths and bidets is investigated through a questionnaire (attached) at 4 weeks after surgery.
10. Secondary endpoint evaluation method – For men over 40 years old, a questionnaire on urinary difficulty is completed and evaluated when visiting the outpatient clinic every week.
11. **Differences from Existing Treatments and Researches**

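### Stopping the device because of pain is not separated from leaving follow-up, so patients who stop before day 7 have no primary value, a selective loss that favours non-inferiority

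*Protocol*

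**What the plan says.** **Exit linked to pain.** Possible Side Effects/Risks and Countermeasures describes a sequence. Pain that the planned analgesics do not control raises suspicion of a complication. Then "It is considered reasonable to identify complications through outpatient care and decide whether to continue the clinical trial". Finally, "If the pain persists despite appropriate treatment, it is thought that the dropout of the patient should be considered".

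**Listed criteria.** Criteria for Discontinuation and Dropout includes "When side effects occur due to anal surgery" and "In case of side effects of sitz bath or bidet", both without qualification. The preceding section says that "side effects from anal surgery may occur, which may vary from pain in the wound to simple infections", so wound pain can itself meet the first of these criteria.

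**Primary endpoint.** Efficacy Evaluation Criteria, Evaluation Method states: "After a week, the degree of pain (after using a sitz bath or bidet immediately after waking up) is used as the primary endpoint".

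**Analysis set.** Data Analysis and Statistical Analysis Method says "The primary endpoint is determined by the FAS". The FAS leaves out only ineligible subjects, subjects never treated and subjects with no data after randomisation. The bias discussion there covers exclusions caused by bidet installation and does not mention exits caused by pain.

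**The concern.** The reasons for leaving overlap with the outcome being measured. One heading covers both discontinuation and dropout, and no sentence says that the pain score is still collected once the assigned procedure stops. Even a patient who keeps attending visits has no primary value by definition if the device was not used that morning.

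The rule is the same in both arms, but its effect is not. If the bidet controls pain less well, more bidet patients reach whatever pain level leads to exit, and more of that arm's high scores disappear. The two observed means move closer together. In a superiority trial this would be conservative. In a non-inferiority trial it raises the chance of accepting an inferior bidet, even with a correct test.

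The per-protocol set offers no cross-check. It requires at least 80% of the scheduled use, so early stoppers are missing there too.

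**Working it through.** **Inputs from Target Number of Subject and Rationale for Calculation:** sitz bath mean 22, SD 3.2, margin 2.2, one-sided alpha 0.025 (z = 1.96), power 80% (z = 0.85), equal allocation.

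**The plan's own figure.** n per group = 2 × [3.2 × (1.96 + 0.85) / 2.2]² = 33.4, rounded up to 34, or 68 in total. This agrees with the protocol.

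**Set-up of the illustration.** The true bidet mean is placed at the margin, 22 + 2.2 = 24.2, so a correct test should declare non-inferiority in 2.5% of trials. Scores are normal with 34 randomised per arm. The test is a two-sample 95% limit against 2.2, so that nothing but the selective loss is at work. Patients who leave are not replaced, because an early leaver with diary data still counts towards the 68 in the FAS. The loss fractions are assumptions, since the protocol gives no dropout rate.

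**Direction, by formula.** If every score above a common cut-off c is lost, the remaining mean is μ − σ·φ(a)/Φ(a), with a = (c − μ)/σ. Take c = 27.26, which removes 5% of the sitz bath arm:

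- Sitz bath: a = 1.645, shift = 3.2 × 0.1031/0.95 = 0.35, remaining mean 21.65.
- Bidet: a = 0.957, loss 16.9%, shift = 3.2 × 0.2524/0.8308 = 0.97, remaining mean 23.23.
- Observed difference: 23.23 − 21.65 = 1.58, against a true 2.2.

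**False non-inferiority rate, by simulation (40,000 trials per cell; 2.5% with no loss):**

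| Cut-off | Sitz bath / bidet above it | Observed difference, all leave | All leave | Half leave | A quarter leave |
|---|---|---|---|---|---|
| 28.6 | 2% / 9% | 1.81 | 7% | 4% | 3% |
| 27.3 | 5% / 17% | 1.57 | 14% | 5% | 4% |
| 26.1 | 10% / 28% | 1.34 | 23% | 6% | 4% |

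**Two further variations:**

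- Exit depends on an earlier pain score correlated 0.5 with the day-7 score (assumption). At the 27.3 cut-off the rate is about 6% if all above it leave and about 4% if half do. Over the three cut-offs, with all leaving, it is 4-7%.
- Only very high pain leads to exit. A cut-off of 31 gives 3.5%. A cut-off of 33.5 (29 + 4.5, the mean plus one SD of the group without sitz baths in the cited study) gives 2.5-2.6%, so practically no inflation.

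**The case against.** **Timing protects much of the endpoint.** Complications are to be identified in outpatient care, and the first scheduled visit is about 7 days after surgery. The primary reading is the 7-8 am diary entry at one week. For many patients, suspicion, work-up, treatment and a decision on dropout would come after that reading. This stands, and it is the main reason the size is uncertain. It does not remove the point. The oral analgesic is planned for 5 days from the afternoon after surgery, so its failure can show before day 7. Some hospitals keep patients for 3 to 4 days, and nothing confines exits to after the reading.

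**The wording is permissive.** A reader might infer that patients with persisting pain must be removed. The text says only that dropout should be considered. The listed side effects carry no such qualifier, but the protocol calls device side effects very rare, so they could not supply losses of the simulated size.

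**The upper-end column is close to a worst case.** It removes everyone above the cut-off and nobody below it, on the day-7 score itself. All three cut-offs also lie below 29, the mean of the group without sitz baths in the cited study. This stands, so 7-23% is an upper-end illustration and not a forecast.

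**The FAS and an SAP may deal with it.** A reader might infer that early leavers fall out of the FAS. They do not if any diary data exist. How a missing day-7 score is handled is commonly left to an SAP and is no fault here. But an SAP cannot recover a score that was never recorded, nor supply a reading that the protocol defines as taken after device use.

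**Silence is not a rule that measurement ends.** That is fair: the protocol does not forbid recording the score. It leaves the matter open, at the point where the loss would be related to the outcome.

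**Conclusion.** The point holds as a gap in the protocol with a known direction and an uncertain size. Exit is tied in part to the primary outcome, continued measurement is not provided for, and the endpoint definition leaves a patient who is off the device before day 7 without a value. Any resulting loss favours non-inferiority when the bidet is truly worse.

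If few or only some high-pain patients leave before day 7, false non-inferiority is about 3-6% in place of 2.5%. The 7-23% range needs every patient above a cut-off to leave before the reading. Both ranges rest on assumed exit fractions, normal scores and the protocol's planning values. The documents do not support a claim that the primary result would be badly distorted. They support a cheap clarification that is worth making, because unrecorded scores cannot be recovered later.

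**What to change.** Leave the clinical criteria for stopping as they are. Add to Criteria for Discontinuation and Dropout, and to the passage on persisting pain, that a patient who stops the assigned procedure stays in follow-up unless consent is withdrawn. In Efficacy Evaluation Criteria, Evaluation Method, state that the day-7 morning VAS is recorded whether or not the device was used that morning. State also that it is analysed in the FAS in the randomised arm. Record whether the device was used, so that the two kinds of reading can be told apart.

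The cost is a few sentences of protocol text and one diary entry after stopping, with a visit already planned at that time. The bidet result may come out slightly less favourable.
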